##### Follow-up

Patients will be telephoned at 3 to 5 days by a study investigator to encourage treatment compliance and EOT visit follow-up. Any deterioration in patient symptoms may be addressed at this visit and a return for clinical assessment may be recommended. The patient will be reviewed at 7 to 10 days after treatment commencement (EOT visit) in the enrolment centre and the area of infection will be measured. At this visit, the patient will be given an SF-36 and ESTI score to complete. A final TOC visit or telephone call will be arranged for 30 days after the enrolment of the patient into the trial.

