##### Secondary outcomes

•Clinical failure: a failure of the initial maximal diameter of infection to reduce by ≥50%

•Clinical relapse: initial improvement in cellulitis at the EOT visit followed by a worsening or re-appearance of cellulitis at the TOC visit.

•Quality of life: the SF-36 and the ESTI score at the EOT visit will be measured.

•Compliance with therapy: the number of unused study medications counted at the EOT visit will be measured.

•Adverse Events: all adverse events will be recorded and submitted to the Irish Medicines Board and the Research and Ethics Committee.

•Microbiological profile: the results of specimens sent for culture to receiving laboratories will be profiled.

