### Sample size, power and statistical methods

Non-inferiority of oral flucloxacillin and placebo relative to oral flucloxacillin and phenoxymethylpenicillin for the above primary and secondary outcomes will be assessed. Sample size per treatment arm is calculated according to an assumed treatment success rate of 85% with oral flucloxacillin and phenoxymethylpenicillin, an equivalence threshold Δ = 12.5% and an α = 0.025 (as this is a non-inferiority study). Sample sizes were calculated using PASS statistical software (Hintze J.(2008) PASS 2008. NCSS, LLC, Kaysville, Utah, USA http://www.ncss.com). Given the preferred study power of 90% for non-inferiority trials, a minimum sample size of 172 in each treatment group is required (n = 344). Non-inferiority will be assessed using a one-sided confidence interval (CI) on the difference of proportions between the two groups. If the upper limit of the CI is less than the equivalence threshold of 12.5%, then non-inferiority is inferred.

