#### Data analysis

Both intention-to-treat (ITT) and per-protocol analysis will be performed. ITT analyses include all patients randomised to the trial regardless of whether they satisfied entry requirements, received the assigned treatments, withdrew from the trial or adhered to the protocol. Missing values will be imputed using a suitable imputation method (last value carried forward or mixed model). A per-protocol analysis includes only patients who completed the full course of treatment and adhered to the protocol requirements. In a non-inferiority trial setting a per-protocol analysis may be more appropriate since it is more likely to reflect actual differences between the two treatments. Furthermore, ITT analysis may be interpreted as being too liberal in a non-inferiority trial and may bias toward making the two treatments appear similar
[24]. As a result, both an ITT and per-protocol analysis will be performed on the resulting data to assess non-inferiority of the placebo/flucloxacillin combination. In particular, to declare non-inferiority, both ITT and per protocol analysis should exclude the non-inferiority margin.

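### Clinical relapse is possible only after improvement at end of treatment, yet a non-inferiority assessment is planned on it; no listed outcome compares sustained cure at day 30 in all randomised patients

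*Protocol article*

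**What the plan says.** Under Secondary outcomes, the protocol article defines clinical relapse as "initial improvement in cellulitis at the EOT visit followed by a worsening or re-appearance of cellulitis at the TOC visit". Clinical failure is a separate item in the same list: "a failure of the initial maximal diameter of infection to reduce by ≥50" per cent.

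Under Follow-up, the EOT visit falls 7 to 10 days after treatment starts. For the test-of-cure (TOC) contact, "A final TOC visit or telephone call will be arranged for 30 days after the enrolment of the patient into the trial".

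Under Sample size, power and statistical methods, non-inferiority of monotherapy "for the above primary and secondary outcomes will be assessed". The method is a one-sided confidence interval on a difference of proportions, and the only margin given is 12.5 points. Under Data analysis, "ITT analyses include all patients randomised to the trial".

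The article gives no denominator for relapse. No listed outcome combines EOT failure with later relapse.

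**The concern.** A patient has to improve before relapse is possible, and improvement by EOT is itself a result of treatment. A between-arm comparison of relapse is therefore conditioned on a state reached after randomisation. Neither natural denominator repairs this:

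- **All randomised patients.** Patients who failed at EOT count as having no relapse. The arm with more failures has fewer patients at risk and can look better for that reason alone.
- **Improvers only.** The arithmetic artefact goes, but the two groups are no longer the randomised ones.

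A second, smaller fault lies in the same definition. The improvement it requires is not linked to the 50% threshold used for cure and failure. A patient whose lesion shrank by 30% at EOT and then worsened is both a clinical failure and a relapse.

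At stake is the question a reader will bring to the day-30 contact: does the cure last on monotherapy as it does on dual therapy? Relapse is the only listed outcome defined by clinical response after EOT, and alone it can point the wrong way.

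**Working it through.** **The plan's own figure.** Inputs from Sample size, power and statistical methods: "assumed treatment success rate of 85% with oral flucloxacillin and phenoxymethylpenicillin", margin 12.5 points, one-sided α = 0.025, power 90%. With unpooled variance,

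n per arm = (1.960 + 1.282)² × 2 × 0.85 × 0.15 / 0.125² = 171.5, rounded up to 172.

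The stated 172 per arm reproduces (power 90.1%) and is not in dispute.

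**Assumptions for the illustration.** EOT cure is 85% on dual therapy (the plan's figure) and 72.5% on monotherapy, that is, worse by exactly the margin (85 − 12.5). Improvement is taken as at least 50% reduction. The relapse rate r among improvers is not in the article; it is set equal in both arms and varied from 5% to 20%.

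**Formulas.**
- Relapse per randomised patient = P(improved) × r. Difference, monotherapy minus dual = (0.725 − 0.85) × r = −0.125r.
- Sustained cure = P(improved) × (1 − r). Difference, monotherapy minus dual = −0.125 × (1 − r).

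| r | Relapse, dual | Relapse, mono | Difference (points) | Sustained cure, dual | Sustained cure, mono | Difference (points) |
|---|---|---|---|---|---|---|
| 5% | 4.25% | 3.63% | −0.6 | 80.75% | 68.88% | −11.9 |
| 10% | 8.50% | 7.25% | −1.25 | 76.50% | 65.25% | −11.25 |
| 15% | 12.75% | 10.88% | −1.9 | 72.25% | 61.63% | −10.6 |
| 20% | 17.00% | 14.50% | −2.5 | 68.00% | 58.00% | −10.0 |

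In every row monotherapy has fewer relapses and a lower rate of lasting cure. At r = 10% and 172 per arm, the expected relapses are 14.6 on dual therapy and 12.5 on monotherapy.

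**Break-even.** If 10% of improvers relapse on dual therapy, monotherapy shows more relapses per randomised patient only once its own rate among improvers exceeds 0.085 / 0.725 = 11.7%.

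**How much the conditioning moves a 12.5-point rule.** The chance that the upper limit for monotherapy minus dual lies below 12.5 points is Φ((0.125 − d)/SE − 1.960), where d is the true difference and SE the unpooled standard error. The responder sets are 0.85 × 172 ≈ 146 and 0.725 × 172 ≈ 125; without selection they are 146 in each arm.

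| Relapse among improvers | Denominator | EOT cure 85% v 72.5% | EOT cure 85% in both arms |
|---|---|---|---|
| 10% v 10% | all randomised | 99.7% | 98.6% |
| 10% v 10% | responders | 92.8% | 94.5% |
| dual 10%, mono 15% | all randomised | 89% | 70% |
| dual 10%, mono 15% | responders | 46% | 49% |

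At 10% in both arms the rule is nearly always met even with no selection at all. Those pass rates come mainly from putting a 12.5-point margin on an event of about 10%. Of these four cases, only the all-randomised one with 15% relapse on monotherapy moves materially. Applied to sustained cure at r = 10% (d = 0.1125, SE = 0.0486), the same rule is met about 4% of the time.

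**The case against.** **The trial's main conclusion is protected.** This stands. In the scenario above monotherapy sits at the margin on the primary outcome, so a single analysis would declare non-inferiority about 2.5% of the time, and the plan requires both the intention-to-treat and per-protocol analyses to exclude the margin. A reader might infer that a favourable relapse result could establish non-inferiority overall. Nothing in the article lets relapse stand in for a failed primary outcome.

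**Failure is listed beside relapse.** This also stands: 27.5% against 15% failures would be visible. But the reader is left to combine the two, and a separate non-inferiority statement on relapse would still be made.

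**The high pass rates are not evidence of conditioning.** Correct. A reader might take 99.7% or 93% as the effect of the definition. The comparison without selection shows otherwise, so those figures should not be used that way.

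**The denominator belongs in the analysis plan.** It may well be settled there, and its absence here is not the complaint. The definition and the intention to assess non-inferiority on it are set in this article, and the difficulty remains under either denominator.

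**The risk set is not exactly the patients with at least 50% reduction.** True. If patients with lesser improvement also count, some failures stay at risk and the difference in relapse may be smaller than tabulated. This weakens the size of the illustration but confirms the overlap between failure and relapse.

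**Tempting extensions.** Three stronger readings are not supported:
- That recurrences treated and cleared before day 30 are missed: the wording can equally mean ascertainment at that contact, and how history is taken there is detail an article commonly omits.
- That mixing visits and telephone calls biases the comparison: the option applies to both arms of a double-blind trial, and no differential effect is shown.
- That improvers on the weaker regimen are easier cases: the article contains nothing on this.

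**Conclusion.** The concern holds as a fault in a secondary outcome. Relapse as defined depends on a post-randomisation state, and the plan attaches a non-inferiority assessment to it. Where monotherapy is 12.5 points worse on EOT cure and relapse among improvers is equal, relapse per randomised patient favours monotherapy by 0.6 to 2.5 points while sustained cure is 10.0 to 11.9 points worse.

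The direction follows from the definition whenever relapse rates among improvers are similar and improvement means the 50% rule. The size rests on the assumed 72.5% cure rate and the assumed 5 to 20% relapse range. The primary outcome, its decision rule and the 172 per arm are untouched. This is a worthwhile and inexpensive improvement, not a threat to the trial's main conclusion.

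**What to change.** 1. Add sustained cure at day 30, in all randomised patients, as the comparative day-30 secondary outcome. Define it as at least 50% reduction at EOT and no worsening or reappearance from EOT up to the day-30 contact, with EOT failures counted as not cured.
2. Tie relapse to patients who met the 50% rule at EOT, so that failure and relapse cannot overlap.
3. Report relapse descriptively beside failure, and limit the sentence on non-inferiority for secondary outcomes so that no such conclusion is drawn on relapse alone.

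The cost is protocol wording and a question on the day-30 form covering the interval since EOT. Treatment and visits do not change, and the Trial status section indicates that enrolment has not begun. The small downside is that sustained cure merges early failure with later relapse, so both components should be tabulated by arm.

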**Methods/design:**

This study is a multicentre, randomised, double-blind, placebo-controlled trial of adults who present to the emergency department (ED) with cellulitis that is deemed treatable on an outpatient basis with oral antibiotics. After fulfilling specified inclusion and exclusion criteria, informed consent will be taken. Patients will be given a treatment pack containing 7 days of treatment with flucloxacillin 500 mg four times daily and placebo or flucloxacillin 500 mg four times daily and phenoxymethylpenicillin 500 mg four times daily. The primary outcome measure under study is the proportion of patients in each group in which there is greater than or equal to a 50% reduction in the area of diameter of infection from the area measured at enrolment at the end-of-treatment visit (7 to 10 days). Secondary endpoints include a health-related quality of life measurement as rated by the SF-36 score and the Extremity Soft Tissue Infection Score (not validated), compliance and adverse events. Patients will be followed up by telephone call at 3 days, end-of-treatment visit (EOT) at 7 to 10 days and test-of-cure (TOC) visit at 30 days. To achieve 90% power, a sample size of 172 patients per treatment arm is needed. This assumes a treatment success rate of 85% with oral flucloxacillin and phenoxymethylpenicillin, an equivalence threshold Δ = 12.5% and an α = 0.025. Non-inferiority will be assessed using a one-sided confidence interval on the difference of proportions between the two groups. Standard analysis including per-protocol and intention-to-treat will be performed.

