### Measures of severity

There are no internationally accepted criteria for ‘mild, moderate and severe’ cellulitis although this classification scheme is widely used in clinical practice
[1]. The classification used by Eron *et al*.
[16], (Table 
1) is useful for guiding treatment decisions for patients with cellulitis. It has been used in local National Health Service (NHS) policy guidelines
[17] and is recommended by the Clinical Resource Efficiency Support Team (CREST) group in Northern Ireland in its consensus statement on the management of cellulitis
[5].

**Table 1 T1:** **Eron classification system for patients with skin and soft tissue infection**[16]

**Class**	**Patient criteria**
**1**	Afebrile and healthy, other than cellulitis
**2**	Febrile and ill appearing, but no unstable comorbidities, or systemically well with comorbidity (PVD, CVI, morbid obesity)
**3**	Toxic appearance, or at least one unstable comorbidity, or a limb-threatening infection
**4**	Sepsis syndrome or life-threatening infection, for example, necrotizing fasciitis

*CVI* chronic venous insufficiency, *PVD* peripheral vascular disease.

The single ‘best antibiotic’ for treating cellulitis is unknown
[1] and thus there is considerable variability in the class, dose and regimen of antibiotic prescribed
[18]. Flucloxacillin either alone or in combination with phenoxymethylpenicillin or its intravenous form, benzylpenicillin, are commonly prescribed in Great Britain and Ireland
[19,20]. Various sources including authoritative textbooks
[21], the national prescribing formulary in the United Kingdom
[22] and local guidelines, provide conflicting information on whether monotherapy with flucloxacillin or dual therapy with combined flucloxacillin and phenoxymethylpenicillin is optimal, particularly for cellulitis treatable on an outpatient basis. Recent evidence has shown that oral phenoxymethylpenicillin prevents cellulitis recurrence in patients with two or more episodes of leg cellulitis
[23].

A study comparing the efficacy, tolerability and compliance of combined oral flucloxacillin and phenoxymethylpenicillin with flucloxacillin alone in the outpatient treatment of cellulitis would provide a valuable resource for clinicians, and may close a gap in the research-based knowledge of this condition.

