#### Outcome measures

##### Primary outcome

The primary outcome measure under study is the proportion of patients treated in each group in which there is greater than or equal to a 50% reduction in the maximal diameter of erythema from the area measured at enrolment to that at the end-of-treatment visit (7 to 10 days).

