##### Measurement of the primary outcome

Clinical cure: Reduction in the area of cellulitis by ≥50% of the initial diameter.

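### Relapse, the only efficacy outcome tied to the day-30 contact, omits residual cellulitis after a 50% response and depends on response at end of treatment, so non-inferiority on it cannot be interpreted alone

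*Protocol article*

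**What the plan says.** The primary outcome is read at the EOT visit, 7 to 10 days after treatment starts. Under Measurement of the primary outcome it is labelled "Clinical cure: Reduction in the area of cellulitis by ≥50% of the initial diameter". Under Secondary outcomes, clinical failure is the complement of this rule and has no time point of its own. Quality of life and compliance are also tied to the EOT visit.

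The Abstract announces a "test-of-cure (TOC) visit at 30 days", and Follow-up adds: "A final TOC visit or telephone call will be arranged for 30 days after the enrolment of the patient into the trial". No measurement is named for that contact. The one efficacy outcome that uses it is clinical relapse: "initial improvement in cellulitis at the EOT visit followed by a worsening or re-appearance of cellulitis at the TOC visit". The word improvement is not defined, and no denominator is given.

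Sample size, power and statistical methods states that non-inferiority "for the above primary and secondary outcomes will be assessed", which includes relapse. Data analysis defines the intention-to-treat (ITT) set as all randomised patients.

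**The concern.** Two gaps follow from the relapse definition.

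**Residual disease is not captured at day 30.** A lesion of 20 cm at enrolment, 10 cm at EOT and still 10 cm at day 30 is a cure by the 50% rule. It has not worsened or re-appeared, so it is not a relapse, and it is not a failure. No listed outcome records that cellulitis is still present.

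**Only EOT improvers can relapse.** A patient who fails at EOT leaves the group at risk. The arm with more failures has fewer patients able to relapse, so a lower relapse proportion may reflect poorer early response and not better late control.

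At stake is the reading of the only late efficacy result. A statement that monotherapy is non-inferior on relapse could be made even where fewer monotherapy patients are free of cellulitis at day 30.

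**Working it through.** **Inputs from the protocol article** (Sample size, power and statistical methods): success 85% with dual therapy, margin 12.5 points, one-sided α = 0.025, power 90%, 172 per arm.

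**Assumptions** (the article gives no figures): relapse risk r among improvers is 5%, 10% or 15% and equal in both arms; improvement means EOT cure; monotherapy cure is 85 − 12.5 = 72.5%, worse by exactly the margin.

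**Step 1. The plan's own figure.** n = (1.960 + 1.282)² × 2 × 0.85 × 0.15 / 0.125² = 171.5, rounded up to 172 per arm. The stated size reproduces, with power of 90.1%. The point made here does not touch it.

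**Step 2. Relapse and sustained cure over all randomised patients.** Relapse = cure × r. Sustained cure = cure × (1 − r).

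| r | Relapse, dual | Relapse, mono | Mono − dual | Sustained cure, dual | Sustained cure, mono | Loss with mono |
|---|---|---|---|---|---|---|
| 5% | 4.25% | 3.63% | −0.6 | 80.75% | 68.88% | 11.9 |
| 10% | 8.50% | 7.25% | −1.25 | 76.50% | 65.25% | 11.25 |
| 15% | 12.75% | 10.88% | −1.9 | 72.25% | 61.63% | 10.6 |

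At r = 10% this is 172 × 0.085 = 14.6 relapses against 172 × 0.0725 = 12.5, about two patients fewer in the worse arm. Monotherapy shows more relapses only if its risk among improvers exceeds 0.85 / 0.725 = 1.17 times that of dual therapy, for example above 11.7% against 10%.

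**Step 3. What a non-inferiority test would show at r = 10%.** The 12.5-point margin is applied to relapse because no other margin is stated.

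- Relapse: SE = √[(0.085 × 0.915 + 0.0725 × 0.9275) / 172] = 0.0290. Upper limit = −0.0125 + 1.96 × 0.0290 = +0.044, or +4.4 points, so it passes.
- Not in sustained cure, 23.5% against 34.75%: SE = √[(0.235 × 0.765 + 0.3475 × 0.6525) / 172] = 0.0486. Upper limit = 0.1125 + 1.96 × 0.0486 = +0.208, or +20.8 points, so it fails.

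**Step 4. Improvers only as denominator.** The groups would be about 172 × 0.85 = 146 and 172 × 0.725 = 125 patients. The lower proportion is no longer forced, but both groups are selected by a result that treatment can affect.

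**Step 5. The plateau.** Suppose both arms have 85% EOT cure and equal relapse, but in one arm a tenth of those cured at EOT still have an unchanged lesion at day 30. That is 0.85 × 0.10 = 8.5% of that arm, or 14.6 of 172 patients. Cure, failure and relapse would be the same in both arms. The tenth is an assumption to show the mechanism, not an estimate.

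**The case against.** The strongest reply is that relapse ordinarily presupposes improvement, that its denominator can be settled in the analysis plan to be agreed before unblinding, and that failures are listed beside it. In the worked case a reader would see failure of 27.5% against 15% next to relapse of 7.25% against 8.5%. The primary test, set exactly at its margin, would pass only about 2.5% of the time. The relapse advantage is small and rests on assumed risks. In the table, sustained cure loses less than the 12.5 points that EOT cure already shows.

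Much of this stands: the misleading direction is slight, depends on an unstated denominator, and cannot overturn the primary result. It does not remove the point. Neither denominator gives an interpretable randomised comparison of relapse alone, and no choice of denominator recovers the plateau patients of step 5, because the definition leaves them out.

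A reader might infer more than the article supports:

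- **That unchanged cellulitis never counts.** It does. A lesion unchanged since enrolment fails the primary outcome and is a clinical failure. Only residual disease after a 50% response is lost.
- **That a late effect of phenoxymethylpenicillin is documented for this trial.** The background says "Recent evidence has shown that oral phenoxymethylpenicillin prevents cellulitis recurrence in patients with two or more episodes of leg cellulitis". Entry here is not limited to recurrent or leg cellulitis, and the article does not claim such an effect by day 30 from a 7-day course.
- **That calling a 50% reduction cure is itself an error.** The term is defined where it is used, so this is labelling.

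**Conclusion.** The point holds in a limited form. The day-30 contact has one efficacy outcome, which misses residual cellulitis after a 50% EOT response and which only improvers can reach. Non-inferiority on relapse is therefore not interpretable on its own. The distortion over all randomised patients is 0.6 to 1.9 points at 85% against 72.5% cure. This assumes a 5% to 15% relapse risk that is equal between arms, and improvement read as EOT cure. If improvement also covers reductions below 50%, failure and relapse overlap and the distortion may shrink, but the plateau gap remains.

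It would be tempting to conclude that the trial could declare an inferior regimen non-inferior through this outcome. The documents do not support that. Relapse is secondary, a declaration needs the ITT and per-protocol analyses to exclude the margin, and neither the primary EOT conclusion nor the sample size changes.

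**What to change.** Add a secondary outcome for all randomised patients: sustained clinical cure at day 30, meaning EOT cure with no residual, worsened or recurrent cellulitis at the index site at the day-30 contact. Count EOT failures as not sustained. Report the difference between arms with a 95% CI. Report relapse descriptively, and make no separate non-inferiority claim on it.

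The cost is outcome wording, one table row and one extra recorded item at a contact already planned: whether any index-site cellulitis remains. When the contact is by telephone the item will be patient-reported, so it is less exact than an examination, and the article should say so. The Trial status section says that enrolment still awaits funding, so no collected data are affected.

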### Randomisation treatments

#### Allocation concealment

A sequentially numbered opaque sealed envelope (SNOSE) will be opened for each patient who consents to enrollment into the study. This envelope will be opaque to intense light. It will contain a copy of the information leaflet, a consent form, an SF-36 and ESTI score, a paper tape measure, the study drugs in two amber containers, and a patient proforma with a unique pre-printed patient identifier to be used throughout the study. The proforma will be inserted in to the ED notes and scanned or stored securely as is standard practice with patient data in the EDs in question. The proforma will then be re-used for the end-of-treatment (EOT) and test-of-cure (TOC) visits. The SNOSEs will be stored in the secure Specialist Registrar Office available in each location, which will be accessible at all times. All study drugs will be packaged by the clinical trial pharmacist who will remain independent of all further patient treatments.

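### SF-36 and ESTI are timed only at the end-of-treatment visit although both forms are in the enrolment envelope; a baseline should be stated and used as a covariate (minor).

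*Protocol article*

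**What the plan says.** Three places in the protocol article bear on the timing of the SF-36 and the Extremity Soft Tissue Infection (ESTI) score.

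- Secondary outcomes: "the SF-36 and the ESTI score at the EOT visit will be measured". No other time point is named.
- Follow-up, on the end-of-treatment (EOT) visit at 7 to 10 days: "At this visit, the patient will be given an SF-36 and ESTI score to complete".
- Allocation concealment lists the contents of the envelope opened for each consenting patient, among them "a consent form, an SF-36 and ESTI score, a paper tape measure". It does not say when the questionnaires are filled in. Re-use at later visits is stated for one item only: "The proforma will then be re-used for the end-of-treatment (EOT) and test-of-cure (TOC) visits".

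The article gives no analysis model for either score. The sample-size section says that non-inferiority will be assessed for the secondary as well as the primary outcomes. The Data analysis section plans to impute missing values by carrying the last value forward or by a mixed model.

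**The concern.** A patient's health before treatment plausibly carries over into a general health score taken 7 to 10 days later. The trial admits Eron Class I and II. By Table 1, that covers people who are well apart from the cellulitis, as well as people who are febrile or have vascular disease, venous insufficiency or morbid obesity. Randomisation is not stratified, so nothing in the design balances these features beyond chance.

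With an enrolment score, the analysis can remove the part of the EOT variation that was present before treatment. Without one it cannot, and no analysis plan written later can recover a measurement that was not taken. Precision matters here because a non-inferiority claim on a continuous score depends on the width of a confidence interval.

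The forms are already in the patient's pack at enrolment. Either they go unused before treatment, or a baseline is intended and the two sections that define the timing leave it out. The text needs correcting in both cases.

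**Working it through.** **The plan's own figure.** The only sample size given is for the binary primary outcome. Inputs: "an assumed treatment success rate of 85% with oral flucloxacillin and phenoxymethylpenicillin", equal true rates in both arms (assumed), a margin of 0.125, one-sided α of 0.025 and 90% power.

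n per arm = 2 × 0.85 × 0.15 × (1.960 + 1.282)² / 0.125² = 171.5, rounded up to 172.

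The stated 172 per arm is reproduced. It was not derived for the SF-36 or ESTI, so here it serves only as the number of patients available.

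**Precision with and without a baseline.** Let the score have standard deviation (SD) 1, with 172 scores per arm and no dropout. Let r be the correlation between the enrolment and EOT scores within arms. The article gives no r, so each value below is an assumption.

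- EOT score alone: standard error = √(2/172) = 0.108 SD; 95% half-width = 1.96 × 0.108 = 0.211 SD.
- EOT score adjusted for the enrolment score (analysis of covariance, large-sample form): standard error = √(2(1 − r²)/172).
- Patients per arm that an unadjusted comparison would need for the same precision: 172/(1 − r²).
- Difference detectable with 90% power at one-sided 0.025: (1.960 + 1.282) × standard error.

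| Assumed r | 1 − r² | Variance saved | 95% half-width (SD) | Equivalent n per arm, unadjusted | Detectable difference (SD) |
|---|---|---|---|---|---|
| no baseline | 1.00 | – | 0.211 | 172 | 0.350 |
| 0.2 | 0.96 | 4% | 0.207 | 179 | 0.342 |
| 0.3 | 0.91 | 9% | 0.202 | 189 | 0.333 |
| 0.5 | 0.75 | 25% | 0.183 | 229 | 0.303 |
| 0.6 | 0.64 | 36% | 0.169 | 269 | 0.280 |

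**Chance imbalance.** With 172 per arm, the difference in mean baseline score has expectation zero and SD √(2/172) = 0.108, so its 95% range is about ±0.21 SD. An imbalance of that size shifts the unadjusted EOT difference by r times its amount: at r = 0.5, 0.5 × 0.211 = 0.106 SD. The unadjusted interval already allows for this on average. What is lost is the means to see the imbalance in a given trial and correct for it.

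**Missing scores.** With one quality-of-life score per patient, taken at EOT, a patient who misses that visit has no earlier score to carry forward. A mixed model likewise has no other measurement of that score to draw on. An enrolment score would give both methods an input, although carrying a pre-treatment score forward to EOT has its own weakness.

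**The case against.** The strongest reply is that the article does not say that no baseline is taken. The Follow-up section describes visits after enrolment and would not be expected to list enrolment procedures. Forms in the envelope are compatible with completion at both visits, and equally with forms packed early for later use. In a condensed article, silence about enrolment is not proof of omission. This stands, and it is why the point is conditional and the first request is to reconcile the sections.

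A reader might infer that the scores will be analysed unadjusted at EOT only. The article does not support that: it says when the scores are measured and gives no model. The choice of model can properly be left to the statistical analysis plan. The collection of a baseline cannot.

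A reader might also infer that the comparison would be invalid, or unable to tell a treatment effect from a chance difference at baseline. That is too strong. Under randomisation the EOT-only comparison is unbiased and has correct error rates. Other severity information is available at enrolment as well: the lesion diameter is recorded, and Eron class has to be judged for eligibility. Some adjustment is therefore possible without a questionnaire, though not for the baseline score itself.

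Finally, r could be low in an acute infection treated for a week, and at r = 0.2 the saving is only 4%. These are secondary outcomes, and the abstract describes the ESTI score as not validated. Both facts limit the weight of the point.

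**Conclusion.** The point holds as a minor, conditional one. Both sections that set the timing name the EOT visit alone, while the enrolment envelope contains the same forms with no instruction on when to complete them. If no baseline is collected, the loss is one of precision and of adjustment for chance imbalance, and no bias follows. Its size cannot be derived from the article: it runs from negligible to about a third of the variance over the correlations considered, assuming equal spread in the two arms, a linear relation and no dropout. The stated imputation methods would also have no earlier quality-of-life value to use. The primary outcome, its sample size and its non-inferiority conclusion are unaffected.

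**What to change.** Reconcile Allocation concealment, Follow-up and Secondary outcomes. State that the SF-36 and ESTI are completed at enrolment before the first dose and again at the EOT visit. In Secondary outcomes, state that the EOT score is compared between arms with the enrolment score as covariate.

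The cost is a few minutes per patient at enrolment, a second copy of each form and one sentence on the comparison. No visit or patient is added. According to Trial status, enrolment still awaits funding, so the change can be made before the first patient is entered.
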